**Drawing:**

This will be a randomized, prospective, clinical trial to be conducted in the Laboratory of Movement Analysis of the Federal University of Juiz de Fora School of Physical Therapy. Participants will be informed about the objectives of the research and those who agree to participate will be asked to sign the informed consent form. After approval from the research ethics committee, the trial will be registered in the Brazilian Clinical Trial Registries (REBEC) platform. Elderly subjects over 60 years of age from both sexes, will be eligible for the study. They will be examined in the geriatric ambulatory service of the university hospital of the Federal University of Juiz de Fora (HUCAS/UFJF). The subjects will be invited for participation by publicizing the study through posters or by invitation of the researcher in the waiting room, during their consultation visits to the ambulatory service. The evaluations will be initiated only after participants sign the Informed Consent Term. After checking for the eligibility criteria for inclusion in the study, the participants will be evaluated for the functional tests: walking speed, sit-up test, and the Timed Up and Go (TUG) test. Body composition will also be evaluated by analysis of the lean mass and fat mass using electrical bioimpedance. In addition, muscle strength during knee extension will be tested. Interviews will be conducted through questionnaires to enquire about their social participation and any fear of falling that they might have. After the 8-week intervention period, all parameters will be re-evaluated. The subjects will be followed up at 3 and 6 months, and re-evaluated through questionnaires about their fear of falling and to check their social participation. Participants will be randomly assigned to one of the two arms of the study, namely, electrostimulation group, or resistance training group. The electro-stimulation group will receive training based on whole-body electrostimulation (WB-EMS). Previous references that showed satisfactory results in the elderly with whole-body electrostimulation, will be used to define the electrostimulation parameters (Kemmler et al, 2014, 2013). The electro-stimulation group will be subjected to 18 minutes of electrical muscle stimulation, two sessions per week, for 8 weeks. The regimen will be as follows: an intermittent bipolar electric current with a frequency of 85 Hz, pulse width of 350 μs with 6 seconds of stimulation and 4 seconds of rest. The thigh, arm, abdomen, thorax, cervical and thoracic paravertebral muscles, and large muscles on the dorsal side will be stimulated. The **Resistance training group** will undergo two training sessions per week, with supervised resistance exercises involving the same set of muscles as those in the electro-stimulation group, but without electro-stimulation. They would be subjected to a load of 50 to 80% of one repetition maximum test (1-RM) for a period of 8 weeks. After the first reassessment, the subjects will be followed up at intervals of 3 and 6 months, and will be evaluated through questionnaires to check their social participation and fear of falling.

**Summary:**

The high prevalence of sarcopenia in the elderly and the role of exercise training in reversing it is well-known. However, there are several limitations that prevent the elderly from adhering to a regular physical training program to increase the muscle strength or mass and to reduce the risk of falls. Recently, whole-body electrostimulation has been reported to be effective for recovery from sarcopenia, with a short period of intervention. This study aims to evaluate the effectiveness of whole-body electrostimulation in improving the function, and muscle strength and mass in the elderly, as well as in reducing their fear of falling and increasing social participation, compared to conventional resistance training. The subjects will be elderly people, with no cognitive and neurological impairment, and no acute or chronic diseases or musculoskeletal ailments that prevent them from performing resistance exercise. The sample will be randomized to two groups. The electro-stimulation group will undergo 18 minutes of electrical stimulation of the muscles, two sessions a week, for eight weeks. The regimen will be an intermittent bipolar electric current with a frequency of 85 Hz, pulse width of 350 μs, with 6 seconds of stimulation and 4 seconds of rest. The resistance training group will perform exercises with a load of 50 to 80% of 1-RM in supervised sessions, twice a week, over a period of 8 weeks. Muscle strength will be evaluated by Microfet manual dynamometer; functional evaluation will be determined by gait speed, TUG test, and sit-up test; muscle mass will be evaluated by electrical bioimpedance, questionnaires will be used to evaluate the fear of falling and degree of social participation. The intergroup data will be compared by paired t-test or Mann-Whitney test according to the tested normality. Longitudinal evaluations after 3 and 6 months of training will be conducted through questionnaires, to evaluate the degree of social participation and the fear of falling. The effect size will be determined for each variable of interest. Analysis of mixed models, including the outcomes measured at the 4 time points (basal, after intervention, 3 and 6 months) will be performed. It is expected that the results of this study will determine the effectiveness of whole-body electrostimulation in improving the functional capacity of the elderly and in reducing the risk of falls.

**Keywords:**

Electrostimulation muscle, aging, sarcopenia.

**Introduction (literature review):**

An increase in the ageing population is a conspicuous worldwide phenomenon. In recent decades, developing countries have seen a progressive decline in their mortality rates and more recently, a decline in the fertility rates, leading to an increase in the elderly population. The definitive expression of this phenomenon can be seen in the population pyramid that is changing from a growing population model to a stabilized population model (Chaimowicz, 1997).

In Brazil, the socio-demographic data from the National Household Sample Survey (PNAD) of the Brazilian Institute of Geography and Statistics (IBGE, 2012) found that in 1991 the elderly represented 4.8% of the population, which increased to 5.8% in 2000, and 7.4% in 2010. Of the total Brazilian population of 190,755,799, the number of those aged 65 years or above is 14,081,480. The Brazilian Institute of Geography and Statistics (IBGE) estimate for the year 2025 is that the elderly are likely to comprise 15% of the total population, corresponding to approximately 30 million elderly in the country (IBGE, 2012). According to the World Health Organization (WHO 2005), by 2025 Brazil will have the sixth largest number of elderly people in the world.

In the country, medical advances and improvements in the general living conditions of the population have increased the life expectancy from 45.5 years in 1940 to 72.7 years in 2008, thus adding 27.2 years to the life expectancy. According to IBGE projections, the average life of its population will continue to increase, reaching 81.29 years in 2050. This is equal to the life expectancy seen today in some countries: Iceland (81.80), China (82.20), and Japan (82.60) (IBGE, 2012). Aging is accompanied by an increase in the prevalence of chronic degenerative diseases and comorbidities, leading to a decrease in the functional capacity, quality of life, and increase in dependence on others (Busscheet *al.*, 2011). Among the changes that occur in the aging process, sarcopenia is significant.

In 1989, Rosenberg proposed the term sarcopenia (from Greek, *sark=* meat; *penia=* loss) to describe the involuntary loss of age-related skeletal muscle mass. Some researchers reported that in addition to the loss of muscle mass, there is also a decrease in muscle strength (Sayeret *al,* 2008; Langet *al*, 2010). Other authors, defined sarcopenia as loss of skeletal muscle mass, muscle strength, and functional limitation (Evans, 1995; Roubenoff, 2001). In 2010, in an attempt to develop an operational definition of sarcopenia, Cruz-Jentoft et *al* proposed through a European consensus that sarcopenia is a geriatric syndrome characterized by loss of muscle mass and muscle function (strength or physical performance), without the need for disease for its appearance, although the process might be accelerated due to some chronic diseases. According to the consensus, muscle mass and strength can be detected in clinical practice by physical examination such as anthropometry and grip muscle strength, and in scientific research with more reliable instruments such as computed tomography and isokinetic dynamometry.

After thirty years of age, the muscle mass decreases by approximately 3-8% and this rate of decline is more pronounced after sixty years (Meltonet *al*, 2000). Baumgartner *et al* in 1998 conducted an epidemiological study to estimate the prevalence of sarcopenia among 883 elderly people in New Mexico. They found an increase in the prevalence of sarcopenia from 13%-24% in those aged above seventy, to 50% in those aged above eighty years. Sarcopenia was significantly associated with physical inactivity, morbidity, obesity, lower income, and change in health behaviors. In 2002, Iannuzzi-Sucich conducted a similar study among 195 women aged 64 to 93 years and found the prevalence of sarcopenia to be 22.6%. The prevalence was 26.8% among 142 men aged 64 to 92 years. Analyzing women and men above 80 years of age, the authors observed that the prevalence increased to 31.0% and 52.9% respectively. Multiple interrelated factors contribute to the development and progression of sarcopenia. It is postulated that with aging, there is a decrease in the level or resistance to anabolic substances in the skeletal muscle, such as testosterone and androgen. In addition, there is atrophy of type II fibers, decline in motor units, loss of alpha motoneurons, reduced protein intake, reduced growth hormone, sedentary lifestyle, and immunosenescence (Roubenoffet *al,* 2000).

Resistance exercise is one of the therapeutic modalities for the prevention and treatment of sarcopenia (Kryger, 2007).

Kruger et al. evaluated 6000 elderly subjects and reported that only 11% were enrolled in resistance training programs. In another study, Sluijs et al. proposed a resistance exercise program for the elderly suffering from chronic pain, and reported that 70% did not show satisfactory long-term compliance. Taylor et al. added that adherence to exercise among the elderly is approximately 14 to 17%. The term adherence refers to the number of sessions held, divided by the number of sessions offered (Hong SY et al, 2008). Data in the literature suggests that the results of an intervention in the elderly are satisfactory when adherence to the program is around 80-85% (Pistersetal, 2010).

Health professionals should make efforts to identify factors impacting adherence to resistance exercises. The elderly tend to participate more regularly at the beginning of the program and the absenteeism increases over time (Pisterset al, 2010). New training strategies might be able to optimize the adherence of the elderly to therapeutic programs. Recently, training with whole-body electrostimulation has been used as an alternative.

Whole-body electrostimulation has been suggested for muscle conditioning in recent times. It is a safe and non-invasive technique using the Mihabodytec® equipment (Gersthofen, Germany) that allows the simultaneous activation of several muscle groups. One of the advantages of WB-EMS is that it acts directly on the synthesis of musculoskeletal protein and demands much lower time than the conventional techniques.

Studies involving the elderly subjects are increasing. In a recent survey, Kemmler et al. (2014) conducted a randomized clinical trial that aimed to evaluate the effectiveness of WB-EMS in changing the body composition of elderly people at the risk of sarcopenia. Seventy-six elderly subjects were allocated to two groups. The experimental group underwent 18 minutes of electro-stimulation, three sessions every 14 days totaling 54 days of intervention. At the end of the program the researchers observed significant results in the experimental group in terms of appendicular muscle mass, lean mass, and in the strength of knee and trunk extenders.

In another study, the effectiveness of WB-EMS in increasing the appendicular muscle mass and abdominal fat in the elderly was investigated. Forty-six elderly subjects with a sedentary lifestyle were allocated to an experimental group (EG) and control group (CG). The EG (n=23) underwent 18 minutes of WB-EMS, three sessions every 14 days totaling 54 days of intervention. After 12 months of intervention, there were statistically significant results in favor of EG in the outcomes of appendicular muscle mass and abdominal fat (Kemmler et al 2013).

Despite promising results, there are few studies investigating the effectiveness of the WB-EMS . Moreover, cultural and socioeconomic influences can impact the results.

**Hypothesis:**

The main hypothesis of this study is that whole-body electrical stimulation is as effective as conventional resistance training in improving clinical-functional health outcomes.

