**Primary objective**

The primary objective of this study is to compare the effect of whole-body electrostimulation and conventional resistance training on functional capacity, muscle strength, walking speed, risk of falling, and lean mass among elderly subjects.

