**Benefits:**

This study will help to determine whether electro-stimulation exercise of the entire body is as effective as resistance exercise (of lifting weights). Thus, participation by volunteers in this research might help in selecting the choice of treatment to improve the strength, muscle mass, and physical capacity of elderly people with sarcopenia who have a high risk of falls and physical disability. The treatment can improve the quality of life for such people. The advantage of this study is that if the effectiveness of electro-stimulation over resistance training is proven, it saves the time required for the process of physical training, because electro-stimulation requires less time than resistance training. Thus, this form of training can provide greater tolerance and increase the adherence among the elderly sarcopenic patients.

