**Data analysis methodology:**

**Statistical analysis**

SPSS version 20.0 will be used. The data will be presented as average and SD or median and interquartile. Statistical analysis by intention to treat will be performed using the unpaired t-test or Mann-Whitney test. The effect size will be determined for each variable of interest. Analysis of mixed models, including the outcomes measured at the 4 time points (basal, immediately after intervention, and at 3 and 6 months) will be performed. The "time point" will be included as a class variable. Group, time, and group * time interactions will be inserted. This will evaluate the sole effect of the intervention, since the difference from baseline values at each time point will be evaluated. A value of p = 0.05 will be assumed for all tests.

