**Sample Size:**

It is expected that 66 elderly people will be involved in the study, 33 in each arm. However, to understand the size of the effect, a pilot study with 10 subjects will initially be conducted to confirm our forecast based on the sample calculation.

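### The main hypothesis claims equal effectiveness, but every planned analysis tests for a difference and no margin is set, so no planned result can support it

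*Protocol*

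**What the plan says.** The Hypothesis section of the protocol gives one main hypothesis: "whole-body electrical stimulation is as effective as conventional resistance training in improving clinical-functional health outcomes". The Benefits section opens on the same claim: "This study will help to determine whether electro-stimulation exercise of the entire body is as effective as resistance exercise". Later, the Benefits section has a conditional sentence that leans towards superiority: "if the effectiveness of electro-stimulation over resistance training is proven". The Primary objective is neutral; the aim there is "to compare the effect of whole-body electrostimulation and conventional resistance training on functional capacity, muscle strength, walking speed, risk of falling, and lean mass".

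The Statistical analysis section fixes the methods. "Statistical analysis by intention to treat will be performed using the unpaired t-test or Mann-Whitney test". A mixed model over the four time points is added: "Group, time, and group * time interactions will be inserted". Also, "The effect size will be determined for each variable of interest". The significance level is 0.05 for all tests, and sidedness is not stated. The section contains no margin, no rule that sets a confidence interval against a threshold, and no equivalence or non-inferiority test.

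The Primary outcome section lists four continuous changes: knee extensor strength, walking speed, sit-to-stand repetitions and lean mass in kilograms. The Sample Size section gives 66 people, 33 per arm. It refers to a sample calculation but shows no effect size, SD, power or margin.

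**The concern.** Equal effectiveness against an active comparator is an equivalence or non-inferiority claim. To support it, the data must exclude a difference large enough to matter, which requires someone to say in advance how large that is. A t-test, a Mann-Whitney test and the group terms of a mixed model do something else: they can reject equality, and if they do not, equality has not been shown. The main hypothesis is thus the null of every planned test. A significant result would count against it or point to superiority, and a non-significant result would leave it open.

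What is at stake is the headline conclusion. If a non-significant p were taken as confirmation, a smaller or noisier trial would be more likely to confirm its hypothesis than a larger and more precise one. With 33 per arm, that would happen often even if electrostimulation were materially worse.

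**Working it through.** **Claim against test**

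| Place in protocol | What it commits to |
|---|---|
| Hypothesis; first sentence of Benefits | Equal effectiveness |
| Primary objective | Neutral comparison |
| Benefits, later sentence | Conditional wording suggesting superiority |
| Statistical analysis | Tests of no difference at 0.05; effect size without interval or threshold |

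The tests fit the Primary objective. They do not fit the Hypothesis.

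**Inputs for the arithmetic.** From the protocol: 33 per arm, alpha 0.05. Assumed: two-sided testing, no dropout, no adjustment for having four primary outcomes, and true differences and margins in units of the SD of the variable analysed (for the primary outcomes, the change). The protocol gives no SD or margin, so a range is shown.

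**The plan's own figure.** The 66 cannot be reproduced, because the inputs to the sample calculation are not given. Solving backwards with n per arm = 2 × ((z for alpha + z for power) / d)², two-sided 0.05, 33 per arm fits d = 0.70 at 80% power: 2 × ((1.960 + 0.842) / 0.70)² = 32.0, which rounds up to 33 when not truncated. It also fits d = 0.80 at 90% power. These are inputs that would fit, not the protocol's own.

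**Precision.** Standard error of the difference = √(2/33) = 0.2462 SD. The critical t on 64 degrees of freedom is 1.998. Half-width of the 95% CI = 1.998 × 0.2462 = 0.492 SD. An observed difference of exactly zero would still be compatible with electrostimulation being about half an SD worse.

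**Chance of a non-significant t-test when the arms truly differ.** Noncentral t, 64 degrees of freedom, noncentrality = d / 0.2462:

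| True deficit (SD) | Noncentrality | P(p > 0.05) |
|---|---|---|
| 0.2 | 0.81 | 87% |
| 0.3 | 1.22 | 78% |
| 0.4 | 1.62 | 64% |
| 0.5 | 2.03 | 48% |
| 0.6 | 2.44 | 33% |
| 0.7 | 2.84 | 20% |

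**Power of 33 per arm for non-inferiority.** True difference 0, one-sided 0.025, noncentral t with noncentrality = margin / 0.2462. The last column is the total N for 80% power from 2 × ((1.960 + 0.842) / margin)² per arm, rounded up; for a 0.5 SD margin this is 62.8, so 63 per arm.

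| Margin (SD) | Power with 66 people | Total N for 80% power |
|---|---|---|
| 0.3 | 22% | 350 |
| 0.4 | 36% | 198 |
| 0.5 | 52% | 126 |
| 0.6 | 67% | 88 |
| 0.7 | 80% | 66 |

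The margin at which 66 people reach 80% power is (1.960 + 0.842) × 0.2462 = 0.69 SD by the normal approximation.

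**The case against.** The strongest reply is that the protocol nowhere says a non-significant p will be reported as equal effectiveness. It states no success rule at all, the Primary objective is only to compare, and the planned tests serve that objective. This stands. A reader might infer that the trial is built to declare success whenever it fails to find a difference, but the text does not say so. What remains is narrower: nothing in the plan can deliver a verdict on the main hypothesis, and nothing guards against the misreading.

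It can also be said that margins and confidence intervals may sit in a statistical analysis plan that is not shown. For interval reporting alone, that would be a fair answer. But the protocol itself fixes the hypothesis, the tests and the sample size, and these do not fit one another. A later document could repair that only by overriding the protocol.

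Three stronger readings are tempting and are not supported:

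- **A separate superiority aim.** The later Benefits sentence is one loose conditional in lay text, in a section that opens with equal effectiveness. It needs rewording, but it is not a further objective.
- **Intention to treat alone pushes towards no difference.** That assumes non-adherence dilutes the contrast. The Introduction and Benefits sections expect adherence to be better with electrostimulation, and unequal adherence could widen or reverse the difference. A per-protocol set is also commonly left to the analysis plan.
- **The pilot will re-size the trial on a between-arm effect from five per arm.** The Sample Size section says "to understand the size of the effect, a pilot study with 10 subjects will initially be conducted to confirm our forecast". It does not say that the ten are randomised or split evenly, or that the effect meant is between arms.

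Finally, the percentages depend on which SD is meant. If margins were set in SDs of the raw measure and the baseline-to-follow-up correlation were 0.8 (assumed), the SD of change would be √(2 × (1 − 0.8)) = 0.63 raw SD. A margin of 0.5 raw SD would then be 0.5 / 0.63 = 0.79 SD of change, and power would be well above 52%. The figures illustrate scale; they are not properties of this trial. The logical mismatch does not depend on them.

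**Conclusion.** The concern holds in this form: the main hypothesis asserts equal effectiveness, all planned analyses test for a difference, and no margin or interval rule is given. Following the plan exactly cannot support the main hypothesis. Reading a non-significant p as equality is a risk that the plan leaves open, not a rule that it states.

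As to size, under the assumptions listed, 33 per arm leaves an interval of about ±0.49 SD. It would miss a true deficit of 0.3 SD in 78% of trials and one of 0.5 SD in 48%. The same sample supports a non-inferiority claim with 80% power only if the margin is about 0.7 SD. Dropout would make these figures worse. Adjusting for baseline would improve them.

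**What to change.** Bring the Hypothesis, Primary objective, Benefits and Statistical analysis sections into line on one claim, before any outcome data are seen.

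- **Wording-only option.** Restate the hypothesis as a comparison or a difference. Report between-group estimates with 95% CIs for each primary outcome. State that a non-significant p will not be reported as equal effectiveness.
- **Keep the equal-effectiveness claim.** Pre-state a justified non-inferiority margin in the units of each of the four primary outcomes, and say whether the claim needs all four. Conclude non-inferiority only where the 95% CI for electrostimulation minus resistance training excludes the margin. State the power that 33 per arm gives: about 52% for a 0.5 SD margin and 80% for 0.7 SD, at true difference 0 and one-sided 0.025.

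The first option costs some text. The second needs a clinical justification of four margins. At the present size it is adequately powered only for a wide margin; on the assumptions above, a 0.5 SD margin at 80% power would take 126 people before dropout. Either way, the conclusion the trial may draw becomes less favourable than the present hypothesis suggests.
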